
### 2.9. Statistical Analysis

#### 2.9.1. Primary Analyses

Each composite score (acceptability, trust, perceived risk) will be analyzed by a mixed repeated-measures ANOVA, with autonomy level (four scenarios) as the within-subjects factor and presentation sequence (four Williams sequences) as the between-subjects factor. The Greenhouse–Geisser correction will be applied when Mauchly’s test indicates a sphericity violation (Huynh–Feldt for ε between 0.75 and 1), and the multivariate approach (Pillai’s criterion) will be reported in parallel as a sphericity-robust check. H1 and H2 will be tested with within-subjects trend contrasts across the autonomy gradient. Because acceptance need not fall in a straight line, the complete set of orthogonal polynomial contrasts—linear, quadratic, and cubic—is pre-specified, and each is reported together with the proportion of the omnibus effect it accounts for. A purely linear profile leaves the quadratic and cubic components negligible, whereas a step between two adjacent levels appears as a large linear component accompanied by a substantial quadratic or cubic one. Because every monotone step is linear-dominant, the polynomial decomposition establishes departure from a straight line but cannot by itself locate the break; the break is identified only from the Holm-corrected adjacent-pair contrasts (A–B, B–C, C–D). A quadratic-dominant profile with a small linear component would instead indicate a non-monotone pattern, which the hypotheses do not predict and which would be reported as such. A non-monotonic or threshold pattern will be reported as such rather than summarized by the linear trend alone. Post hoc comparisons use dependent-samples *t*-tests for the six scenario pairs with Holm’s sequential correction, applied within each hypothesis-defined family of tests in line with current guidance on multiplicity control [74]. Effect sizes will be reported as partial η^2^ for omnibus tests and Cohen’s dz for pairwise comparisons, with 95% confidence intervals, following effect-size-centered reporting recommendations [64]. Assumption checks include graphical inspection of difference-score distributions; as a distributional robustness analysis, the Friedman test with Holm-corrected Wilcoxon signed-rank pairwise comparisons will be reported alongside each primary test—supplemented by ordinal (cumulative-link) models as sensitivity analyses for the Likert-based outcomes [71]—and the concordance of parametric and nonparametric conclusions stated explicitly. Order dependence is tested directly as the scenario × sequence interaction; a non-significant interaction, together with equivalence of the four sequence-specific profiles, supports pooling across sequences. Independently of that test, the autonomy effect is re-estimated from a linear mixed model with random intercepts per participant and additive fixed effects of autonomy level and serial position (1–4). The Williams square renders this model identified, so the estimate is adjusted for arbitrary—not merely linear—serial-position and fatigue effects, while first-order carry-over is balanced by the design rather than modeled; position-adjusted and unadjusted estimates are reported side by side, and any material divergence between them is treated as evidence of an order artifact and interpreted accordingly. Perceived difficulty (DIF1) and perceived technical sophistication (MAN2) are each added as time-varying covariates in further sensitivity models, addressing fatigue and the possibility that responses track the apparent complexity of the system rather than its autonomy. Finally, between-person heterogeneity in response profiles is examined by adding a random slope for the linear autonomy contrast and testing the improvement in fit by a likelihood-ratio test; a substantial random-slope variance indicates that an average trajectory conceals distinct response patterns and licenses the exploratory typology described in Section 2.9.2. Because a non-significant test is not evidence of absence, a smallest effect size of interest of *dz* = 0.20—the value detectable at the Bonferroni bound for the six pairwise contrasts at *N* = 300—is fixed in advance, and equivalence testing by two one-sided tests against that bound is reported alongside every null pairwise result, so that any claim that two adjacent scenarios do not differ rests on an equivalence test rather than on the absence of significance.

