
#### 2.9.2. Secondary and Exploratory Analyses

(i) Moderation (H4): the scenario × AI familiarity (B1, centered) interaction, via repeated-measures ANCOVA or a linear mixed model with random intercepts per participant, the recommended framework for vignette data [62]; presentation sequence is retained as a between-subjects factor here, as in every repeated-measures model in this protocol. (ii) Person-level multiple regression: mean acceptability across scenarios predicted by AI familiarity, general AI attitudes, and demographics (reporting *B*, *SE*, β, 95% CI, R^2^, VIF). (iii) Responsibility migration (H3): a 4 × 4 mixed ANOVA (scenario × actor, RES1–RES4, both within-subjects; presentation sequence between-subjects) with Greenhouse–Geisser correction; the scenario × actor interaction is the direct test of H3. Because H3 is confirmatory, it receives the same order controls as H1 and H2: the sequence terms are inspected first, and the migration estimate is repeated in a linear mixed model containing an additive serial-position term. (iv) Responsibility concentration: a normalized Herfindahl–Hirschman index computed per scenario from the relative weights of the three responsible actors (surgeon, hospital, AI developer; RES4—unavoidable medical uncertainty—is not a responsible actor and is analyzed separately), compared across scenarios by mixed repeated-measures ANOVA with sequence as a between-subjects factor; low values index diffusion of responsibility across actors, operationalizing the “problem of many hands” described in the responsibility literature [44,45]. (v) RES5 (moral duty) and RES6 (outcome-independent accountability): mixed repeated-measures ANOVAs across scenarios with sequence as a between-subjects factor, Holm-corrected within the family. (vi) Global preference (P1): a goodness-of-fit chi-square with standardized residuals over six analysis categories on 5 degrees of freedom. The six categories are the four scenarios, “I would prefer AI not to be involved in any way,” and a combined “no clear preference” category; the last pools the item’s two undecided options (“I have no preference” and “I cannot decide”), which are combined a priori because neither expresses a preference between scenarios and each is expected to be sparse. Consistency between stated preference and each participant’s maximum-acceptability scenario is reported descriptively. (vii) Exploratory: P4a and P4b (the surgeon’s permanent legal and, separately, moral responsibility) analyzed descriptively, compared with each other by a dependent-samples test on the within-person difference, and correlated with RES5/RES6; free-text concerns (P2) summarized by brief thematic analysis. (viii) Sensitivity analyses: primary analyses repeated (a) excluding participants with a single attention-check failure (who are retained under the primary rule) and (b) excluding participants with any comprehension failure, to demonstrate that conclusions do not depend on the cleaning criteria [69]. (ix) Order effects: descriptive profiles by sequence, the scenario × sequence interaction with its effect size and 95% confidence interval, and sequence-specific manipulation-check profiles. (x) Response-pattern typology (exploratory): where the random-slope test of Section 2.9.1 indicates heterogeneity, individual acceptability trajectories across autonomy levels are classified by latent-class growth analysis, with class enumeration by BIC and entropy and a minimum class size of 5% fixed in advance, and class membership described against AI familiarity, healthcare-system trust, and demographics; no inferential claim is attached to this analysis. (xi) Healthcare-system trust (B6) enters the person-level regression of (ii) as a covariate and is examined as an exploratory moderator of the autonomy effect, alongside healthcare contact frequency (B5) and prior surgical experience (B4, B4a). (xii) Subgroup analyses, all of which are secondary or exploratory, are governed by a minimum-cell rule fixed in advance: inferential tests within a subgroup are reported only where that subgroup contains at least 50 valid participants, the size at which a within-subject difference in *dz* = 0.40 is detectable at power 0.80; subgroups of 30–49 are reported descriptively with 95% confidence intervals and labeled as underpowered; subgroups below 30 are pooled into a residual category or not reported. A difference between subgroups is never inferred from a significant effect in one and a non-significant effect in another; only the formal interaction term, with its own confidence interval, supports such a claim. The set of moderators is fixed a priori, in the pre-registration, to seven: AI familiarity (B1), healthcare-system trust (B6), healthcare contact frequency (B5), prior surgical experience (B4/B4a), education (D3), age (D2), and field of activity (D4). Results are reported for all seven irrespective of significance, and no further moderator is added after the data are seen. (xiii) Missing data: because all closed items are mandatory, missingness in the dependent variables is structurally impossible within a submitted questionnaire. Two other forms of missingness remain. The first is unit-level, from questionnaires abandoned before submission. The platform is configured not to store partial submissions, so responses from abandoned questionnaires are neither retained nor analyzed (Section 2.10 and Appendix A.1). Attrition is therefore characterized from the platform’s page-level counters—how many participants reached each page—rather than from partial response data, and is reported as drop-out by serial position in the participant-flow diagram. Analyses are accordingly restricted to complete cases, that is, participants with all four scenario blocks, and no imputation is performed: with no partial records retained, there are no incomplete cases to impute. The second is item-level, on the background and demographic items that offer a “prefer not to answer” option or, in the case of B4 and B4a, are not displayed where the explicit health-data consent is declined; these are treated as a distinct category descriptively and as missing in inferential models, with a sensitivity analysis retaining the category in the person-level regression. Because complete-case analysis is not neutral when attrition is differential, drop-out is compared across the four presentation sequences, and any imbalance is reported and carried into the interpretation of the order analyses. All tests are two-tailed at α = 0.05, with exact *p*-values, effect sizes, and 95% confidence intervals reported for all tests, including non-significant ones. On closed 1–7 scales, no distribution-based outlier removal is applied.

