## 3. Expected Results

Based on the algorithm-aversion and trust studies [19,37,38], we expect acceptability and trust to decline—and perceived risk to rise—across the autonomy gradient from Scenario A to Scenario D, with the largest drop anticipated at the transition to autonomous planning (Scenario D), where the surgeon’s corrective role is described as residual. Whether that decline is a gradient or a step is an open question that the design is equipped to address: a step would show as a substantial quadratic or cubic component alongside the linear one, and its location would be identified by the adjacent-pair contrasts, which we expect to place the largest single drop at C–D. Nor do we assume the pattern is homogeneous across participants; a substantial random-slope variance would itself be informative, indicating that an average trajectory conceals distinct groups of respondents rather than describing a shared response. The expectation of decline is, in any case, consistent with survey evidence that public comfort is conditional on physician supervision [24,25,31]. For responsibility attribution, we expect the surgeon to be assigned the dominant share in low-autonomy scenarios [41], with a progressive migration toward the AI developer—and possibly a diffusion of responsibility across actors, indexed by falling Herfindahl concentration—as autonomy increases [44,45]. We expect the manipulation check (perceived AI control) to order the scenarios from A to D within each of the four presentation sequences, validating the experimental gradient independently of serial position, and we expect no scenario × sequence interaction. Should one nevertheless appear, the position-adjusted mixed-model estimate becomes the primary basis for interpreting H1–H3, and the magnitude of the order effect will itself be reported as a finding about the stability of vignette-based autonomy judgments. Given the design’s sensitivity (power of 0.99 against small within-subjects effects at ρ = 0.50, and 0.95 at ρ = 0.30, for the target sample), a null result for a primary hypothesis would place a tight upper bound on the size of any autonomy effect rather than leaving the question open; the pre-specified equivalence tests of Section 2.9.1 make that bound explicit rather than infer absence from non-significance [70]. The moderation hypothesis (H4) is powered only for medium-small interactions and will be interpreted with corresponding caution. Results will inform the ordering of public concerns along the assistance-to-autonomy continuum and identify which implementation configurations are publicly acceptable entry points for surgical AI in Romania.

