Trust in the healthcare system	B6	Likert 1–7	Covariate/exploratory moderator
Manipulation check (technical sophistication)	MAN2, per scenario (×4)	Likert 1–7	Design validation/covariate
Presentation sequence	SEQ	4 categories	Between-subjects design factor
Serial position of scenario	POS	1–4	Covariate (order, fatigue)

Abbreviations: DV, dependent variable; ACC, acceptability items; TRU, trust items; RSK, perceived-risk items; RES, responsibility items; MAN1 and MAN2, manipulation-check items; DIF1, perceived-difficulty item; ATT1 and ATT2, attention checks; CC_A–CC_D, comprehension checks; B1–B6, background items; G1–G4, general-attitude items; P1–P4b, preference items; D1–D7, demographic items; SEQ, presentation sequence; POS, serial position of the scenario; H1–H4, hypotheses 1–4.

**Table 5 healthcare-14-03030-t005:** Hypothesis-by-hypothesis analysis plan.

Hypothesis/Objective	Planned Test	Reported Coefficients
Manipulation validation	Mixed RM-ANOVA on MAN1 (autonomy within × sequence between) + polynomial trend contrasts; the intended ordering A → D expected within every sequence	*F*, corrected *df*, *p*, partial η^2^; ε(GG)
H1. acceptability and trust decline with autonomy	Mixed RM-ANOVA per composite, sequence as between-subjects factor (Greenhouse–Geisser) + orthogonal polynomial trend contrasts (linear, quadratic, cubic); post hoc dependent *t*-tests, Holm correction	*F*, corrected *df*, *p*, partial η^2^ (90% CI); pairwise dz (95% CI)
H2. perceived risk increases with autonomy	Mixed RM-ANOVA (autonomy within × sequence between) + orthogonal polynomial trend contrasts; post hoc dependent *t*-tests, Holm correction	*F*, corrected *df*, *p*, partial η^2^; pairwise *dz*
H3. responsibility migrates surgeon → AI developer	4 × 4 mixed ANOVA (scenario × actor within, sequence between), Greenhouse–Geisser; the scenario × actor interaction is the test of H3; repeated with a serial-position term	*F*, corrected *df*, *p*, partial η^2^; ε(GG)
Responsibility concentration	Normalized Herfindahl–Hirschman index (RES1–RES3) per scenario, compared by mixed RM-ANOVA (sequence between)	Mean HHI per scenario; *F*, *p*, partial η^2^
Moral–legal distinction	Mixed RM-ANOVAs on RES5 and RES6 across scenarios (sequence between); Holm correction within family	*F*, corrected *df*, adjusted *p*, partial η^2^

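### The additive serial-position term in the H3 mixed model cannot change any scenario × actor estimate, so H3 does not get the position control that H1 and H2 get

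*Protocol article*

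**What the plan says.** Section 2.9.2(iii) sets up a mixed ANOVA with scenario and actor (RES1–RES4) within subjects and sequence between subjects, in which "the scenario × actor interaction is the direct test of H3". It then claims parity with the other confirmatory hypotheses: "Because H3 is confirmatory, it receives the same order controls as H1 and H2". Two controls follow. The sequence terms are looked at first, and "the migration estimate is repeated in a linear mixed model containing an additive serial-position term". Table 5 repeats this: "the scenario × actor interaction is the test of H3; repeated with a serial-position term". Neither place mentions a position × actor term.

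The model being carried over is in Section 2.9.1. There each participant has one composite score per scenario, and the fixed effects are autonomy level and four-level serial position, with a random intercept per participant. Adjusted and unadjusted estimates are shown side by side, and "any material divergence between them is treated as evidence of an order artifact".

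Section 3 gives the adjusted model a decisive role. If a scenario × sequence interaction appears, "the position-adjusted mixed-model estimate becomes the primary basis for interpreting H1–H3".

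**The concern.** For H1 and H2 there is one outcome per scenario, so an additive position effect can be confused with the scenario effect, and an additive term can remove it. For H3 the quantity of interest is a difference between actors. All four actors are rated in the same block and therefore at the same position. A position effect common to all actors does not touch H3. Only one that differs by actor can distort it, for example a growing tendency to blame the developer as blocks accumulate, and the stated model has no term for that.

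The stake is that a confirmatory hypothesis is described as position-adjusted when its estimate is not. Agreement between the two sets of H3 estimates would look reassuring but carry no information. If order dependence is found, the estimate promoted to primary for H3 would be the unadjusted one under another name.

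**Working it through.** The plan gives no figure for this adjustment, so there is none to reproduce.

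**Inputs.** From the protocol: the sequences ABCD, BDAC, CADB and DCBA (Section 2.1), with analyzed sizes n1 to n4 in that order; N = 300; four actors. Assumed, because the protocol gives no values: the sequence sizes after drop-out and exclusions, and a drift per position of +d for the developer and −d for the surgeon.

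**Step 1: the additive term cancels.** Write the stated model for participant i, scenario s, actor a as

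y = μ + S(s) + A(a) + SA(s,a) + P(position of s for i) + u(i) + e.

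Within one block, developer minus surgeon is

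[A(dev) − A(sur)] + [SA(s,dev) − SA(s,sur)] + error difference.

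P and u both drop out. Every scenario × actor contrast is built from such within-block differences, so P cannot alter it at any sequence sizes.

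**Step 2: check by fitting.** Random-intercept models were fitted to simulated data (300 participants × 4 scenarios × 4 actors). Adding additive position moved none of the 9 interaction coefficients by more than 10⁻¹² at 75/75/75/75, 95/75/70/60 or 120/70/60/50. Position × actor moved them by up to 0.13 and 0.27 at the two unequal splits. At 95/75/70/60 the additive term lowered the residual variance from 1.283 to 1.235 and raised the interaction F from 82.2 to 85.3, with the estimates unchanged.

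**Step 3: size of the bias.** D's position minus A's position is +3, −1, +1 and −3 in the four sequences. Its mean over participants is [3(n1 − n4) + (n3 − n2)]/N. The drift enters developer minus surgeon as 2d per position, so the bias in the D–A change of that difference is

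2d[3(n1 − n4) + (n3 − n2)]/N.

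- 75/75/75/75: 0 for any d.
- 80/75/75/70, d = 0.1: 0.2 × 30/300 = 0.02.
- 90/75/75/60, d = 0.1: 0.2 × 90/300 = 0.06; d = 0.2: 0.12.
- 100/75/75/50, d = 0.1: 0.2 × 150/300 = 0.10; d = 0.2: 0.20.

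**Step 4: noise-free confirmation**, with d = 0.2 and a true D–A change in developer minus surgeon of 3.100:

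| Sequence sizes | No position | Additive position | Position × actor |
|---|---|---|---|
| 75/75/75/75 | 3.100 | 3.100 | 3.100 |
| 95/75/70/60 | 3.233 | 3.233 | 3.100 |
| 120/70/60/50 | 3.367 | 3.367 | 3.100 |

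The formula gives the same excess: 0.4 × 100/300 = 0.133 and 0.4 × 200/300 = 0.267.

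**Step 5: the same term does work for H1 and H2.** With a single outcome per scenario, a common position effect of 0.2 per position and sizes 95/75/70/60, the D–A estimate is 0.267 without position and the true 0.200 with it.

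**The case against.** **The migration estimate is not defined.** If it meant a developer-minus-surgeon score per scenario, an additive position term would adjust it properly (3.233 becomes 3.100 at 95/75/70/60). That is correct, and it is one of the remedies below. But no such score is named anywhere; Section 2.9.2(iii) and Table 5 both tie H3 to the interaction, and Table 5 says it is that test which is repeated with a position term.

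**H3 has other order control.** A reader might infer that H3 has none. The protocol does not support that. The Williams square balances position when sequences are equal, allocation is random in equal proportions, and balance is monitored during accrual. The ANOVA's sequence terms include scenario × actor × sequence, which can show an actor-specific order effect. Weighting the sequences equally also gave 3.100 at every split, although the protocol does not state a weighting. This protection stands, but it is not the position adjustment that the plan describes and, in Section 3, relies on.

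**Bias needs two conditions together.** It requires drift that differs by actor and unequal analyzed sequences. That also stands. The larger splits are fairly extreme: Table 3 expects about 445 eligible, or 111 per sequence, so 100/75/75/50 would mean about 90% of one sequence and 45% of another yielding valid records. Under chance imbalance alone, the position difference has variance (9 + 1 + 1 + 9)/4 = 5 per participant. At d = 0.1 the bias then has a standard deviation of 0.2 × √(5/300) ≈ 0.026 points. Differential drop-out, which Section 2.9.2(xiii) itself anticipates, could exceed this.

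**Results are not wholly identical.** F and p move slightly with the residual variance. The estimates do not.

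**Conclusion.** The point holds as a statement about the model. The additive position term leaves every scenario × actor estimate exactly as it was, so the claim of the same order controls is wrong for the position adjustment. Side-by-side H3 estimates cannot diagnose an order artifact, and the Section 3 fallback adds no position correction for H3. This part rests on algebra and needs no assumption about drift or imbalance.

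A reader might go further and conclude that the H3 result will be biased, or that the fallback is always worse than the mixed ANOVA. Neither follows. With equal sequences, or with drift common to all actors, H3 is unbiased under either analysis. Where both conditions hold, the illustrative bias is 0.02 to 0.20 points on a 1–7 scale across the splits and drifts in Step 3, all of them assumed. The matter is worth correcting because H3 is confirmatory and the stated safeguard does not do what the plan says.

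**What to change.** Before pre-registration:

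- In Section 2.9.2(iii) and Table 5, replace the additive term in the H3 mixed model with position × actor (four-level position). Alternatively, fit the per-scenario difference RES3 − RES1 with scenario and four-level position; this covers the surgeon–developer pair that H3 names.
- Name scenario × actor × sequence as the order test for H3. Position is determined by scenario and sequence together, so an actor-specific position effect appears in that term.
- In Section 3, refer the H3 fallback to the corrected estimate and tie it to that three-way term.

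The cost is wording and a line of code. Position × actor uses up to 3 × 3 = 9 more fixed-effect degrees of freedom, against 300 × 16 = 4800 ratings. Serial position is already kept in the dataset (Section 2.11, Table 4), so no new data are needed.

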The per-scenario response block contains nine Likert items measuring the three primary dependent variables—acceptability (ACC1–ACC3), trust (TRU1–TRU3), and perceived risk (RSK1–RSK3)—followed by six responsibility items (RES1–RES4: surgeon, hospital, AI developer, unavoidable medical uncertainty; RES5: the surgeon’s moral duty to verify AI outputs; RES6: outcome-independent accountability), two manipulation-check items (MAN1: perceived AI control over the final surgical decision; MAN2: perceived technical sophistication of the system), and a perceived difficulty item (DIF1). All scaled items use 7-point end-anchored Likert response formats. Composite scores are computed as the arithmetic mean of their items after reverse-scoring RSK1 (8 − score), which is the only reverse-keyed item in the response block; higher risk scores indicate higher perceived risk. Treating item means on end-anchored 7-point scales as quasi-continuous interval variables is standard practice in experimental vignette research; ordinal-model sensitivity analyses are nevertheless planned in line with current guidance on Likert-based outcomes [62,71]. Table 4 summarizes the measurement structure; per-scenario variables carry the scenario suffix (e.g., ACC1_A, ACC1_B, ACC1_C, ACC1_D).

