Because everyday usage collapses several distinct notions into one, the instrument separates them explicitly, and the header shown to participants states the intended sense. RES1–RES3 measure agent-directed responsibility—how much of the responsibility for an error each party should bear—and appear, together with RES4, under a common header that states that responsibility may be shared and that each party is to be rated separately rather than as a share of a fixed total, so that both diffusion and concentration are expressible; the header also glosses responsibility as answering for the error and putting it right, expressly distinguishing it from being found at fault in court. RES4 is not an agent and captures the alternative attribution that an error reflects irreducible clinical uncertainty; it is analyzed separately and is excluded from the concentration index. RES5 isolates moral responsibility from legal fault by construction (“even if the surgeon were not legally at fault…”), and RES6 isolates accountability in its outcome-independent sense—whether answerability depends on how the operation turned out—which is precisely what separates accountability from outcome-based blame. Legal liability proper is not measured per scenario. It is asked once, globally, and separately from the ethical claim, as two items presented on the same page and scale: P4a, that the surgeon should always remain legally responsible for any surgical outcome, and P4b, that the surgeon should always remain ethically responsible for it. Keeping them apart matters because a single double-barreled item would force the two notions to move together and would conceal exactly the pattern the responsibility literature predicts—a surgeon held morally answerable for an outcome to which no legal fault attaches. Both are analyzed descriptively and against RES5 and RES6, and their difference within participants—the extent to which a respondent holds the surgeon morally but not legally answerable—is itself reported. They are not treated as within-scenario outcomes, because lay judgments of legal liability depend on doctrinal assumptions that a short vignette cannot supply and that vary with the respondent’s exposure to the legal system; treating such judgments as a repeated-measures outcome would attribute a precision to them that they do not have. The Romanian wording of these items avoids the terms “culpă” and “răspundere juridică” except where legal fault is explicitly intended, and the pilot cognitive interviews (Section 2.8) probe specifically whether participants read RES1–RES3 as moral answerability, as causal contribution, or as legal liability. If the interviews reveal systematic conflation, the header wording will be revised, and the items retested before pre-registration, and the change documented.

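### The responsibility-concentration index falls when all three ratings rise equally, so reading every low value as diffusion can mislabel a change in overall level

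*Protocol article*

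**What the plan says.** Section 2.9.2(iv) of the protocol article defines the measure as "a normalized Herfindahl–Hirschman index computed per scenario from the relative weights of the three responsible actors". It is compared across scenarios by a mixed repeated-measures ANOVA with sequence between subjects, and the reading rule is that "low values index diffusion of responsibility across actors". Table 5 names the inputs: "Normalized Herfindahl–Hirschman index (RES1–RES3) per scenario". RES4, unavoidable medical uncertainty, is left out: "it is analyzed separately and is excluded from the concentration index".

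The ratings are described in Section 2.6. On format: "All scaled items use 7-point end-anchored Likert response formats"; Table 4 gives the range as 1–7. On how they are elicited, the header shown to participants says that "each party is to be rated separately rather than as a share of a fixed total, so that both diffusion and concentration are expressible". Section 2.6 states a transformation for RSK1 (8 minus the score) but none for RES1–RES3.

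Section 3 expects that responsibility may diffuse across actors as autonomy increases, "indexed by falling Herfindahl concentration".

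**The concern.** A Herfindahl index measures how unevenly a total is divided, so it needs quantities whose zero means none and whose sum is meaningful. RES1–RES3 offer neither. The scale starts at 1, and participants are told that their ratings need not add up to anything. Dividing each rating by the sum brings the overall level of the three ratings into a measure that is meant to describe only how responsibility is spread.

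This matters because the distortion can run in the direction the protocol expects. If participants hold every party more responsible in the autonomous scenario, the index falls even when the point differences between surgeon, hospital and developer stay the same, and the stated rule calls that diffusion. At the other end, a participant who gives all three parties the minimum also scores 0 and is read as maximally diffuse. If the lowest anchor means no responsibility, that response is a responsibility gap, which is a different finding from shared responsibility.

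**Working it through.** **Inputs.** Three ratings r₁, r₂, r₃, each 1 to 7 (Section 2.6, Tables 4 and 5). The protocol gives no numerical value or range for the index, so there is no stated figure to reproduce. The share formula is not written out; the natural reading is used here.

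**Formulas.** sᵢ = rᵢ / (r₁ + r₂ + r₃); H = Σsᵢ²; normalized index = (H − 1/3) / (1 − 1/3).

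For three actors this equals SD² / (3 × mean²), where SD (divisor 2) and mean are those of the person's three ratings. Adding a constant to all three ratings leaves the SD unchanged and raises the mean. The index must therefore fall whenever the ratings are unequal.

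**Equal additive rise, worked.**

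- (5,2,2): sum 9; H = (25 + 4 + 4)/81 = 0.4074; index = (0.4074 − 0.3333)/0.6667 = 0.111. Mean 3, SD 1.73.
- (7,4,4): sum 15; H = (49 + 16 + 16)/225 = 0.3600; index = (0.3600 − 0.3333)/0.6667 = 0.040. Mean 5, SD 1.73.
- Relative fall: (0.111 − 0.040)/0.111 = 64%, with every gap and the SD unchanged.

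**How general this is.** Of the 7³ = 343 patterns, 6³ = 216 have room for a one-point rise in all three ratings. The index falls in 210. It stays at 0 in the 6 all-equal patterns and never rises.

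**It can move against the gaps.** From (4,1,1) to (7,3,3) the lead of the first actor widens from 3 to 4 points, yet the index falls from 0.250 to 0.095.

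**All-equal patterns.** (1,1,1), (4,4,4) and (7,7,7) all give H = 1/3 and index 0.

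**Ceiling.** The largest value over all 343 patterns is at (7,1,1): H = 51/81 = 0.6296; index = 0.444.

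**Recoding to 0–6 as a possible cure.**

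| Pattern | Index on 1–7 | Index on 0–6 |
|---|---|---|
| (7,1,1) | 0.444 | 1.000 |
| (2,1,1) | 0.063 | 1.000 |
| (5,2,2) | 0.111 | 0.250 |
| (7,4,4) | 0.040 | 0.0625 |
| (7,7,7) | 0 | 0 |
| (1,1,1) | 0 | undefined (0/0) |

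Recoding restores the 0–1 range. But the fall from (5,2,2) to (7,4,4) becomes (0.250 − 0.0625)/0.250 = 75%, larger than before, because the same SD is divided by a smaller mean. It also gives (2,1,1), one point above the floor, the same score as (7,1,1). A one-point rise still lowers the index in 210 of the 215 defined patterns.

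**The case against.** The strongest reply is that the index is defined on relative weights, and those do become more even from (5,2,2) to (7,4,4): the leading actor's share goes from 5/9 = 56% to 7/15 = 47%. A proportional rise in all three ratings would leave the index unchanged. This stands, so it would be wrong to say that the distribution has not changed in any sense. What remains is that ratios of these ratings have no clear meaning when the scale has no true zero, while differences do. Section 2.6 itself treats item means on this response format as interval variables.

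A second reply is that level is analyzed elsewhere. The scenario × actor ANOVA in Section 2.9.2(iii) would show a general rise as a scenario effect. That is so, but nothing ties the reading of the index to it. An equal rise adds nothing to the scenario × actor interaction in (iii), yet (iv) would call it diffusion.

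A third reply is that the formula may stand in a statistical analysis plan that is not shown. The point is not that a formula is missing. The article fixes the inputs, the type of index and the reading rule, and level dependence holds on the 1–7 and the 0–6 scale alike.

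Three stronger inferences are tempting, and the documents do not support them:

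- **The 0.444 ceiling invalidates the comparison.** It applies equally in all four scenarios and does not bias within-person contrasts. It is a scale matter only.
- **H3 is compromised.** Its test is the scenario × actor interaction on the ratings, which does not use the index.
- **(1,1,1) certainly means nobody is responsible.** The anchor wording of the items is not shown, so this is an assumption.

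**Conclusion.** The point holds for a secondary analysis. On the natural reading of Section 2.9.2(iv) and Table 5, the index mixes how evenly responsibility is spread with how high the ratings are overall. An equal additive rise lowers it for every unequal pattern, by 64% in the example, and all-equal patterns score 0 at any level. The rule that low values mean diffusion is therefore too broad.

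The conclusion assumes that shares are formed from the ratings as collected, which is inferred from the absence of any stated rescaling. The part about nobody being responsible also assumes that the lowest anchor means none. How large the distortion would be in the study depends on how far the overall rating level shifts between scenarios. The documents give no figure for that, so the examples show what can happen and do not predict a size. H1, H2 and the H3 test are untouched.

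**What to change.** In Section 2.9.2(iv) and Table 5, before pre-registration:

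1. State the share formula.
2. Report per scenario, beside the index, the within-person SD of RES1–RES3, which an equal additive shift leaves unchanged, and the total RES1 + RES2 + RES3.
3. Report the proportion of all-minimum patterns per scenario as a separate category, not counted as diffusion.
4. Call a fall in the index diffusion only if the SD also falls.

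The SD condition is necessary but not sufficient. From (7,1,1) to (4,1,1) both measures fall (index 0.444 to 0.250, SD 3.46 to 1.73) although one actor alone is still rated above the minimum. The SD is also 0 for both (1,1,1) and (7,7,7). This is why the total and the all-minimum proportion must stand beside it.

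Do not rely on recoding to 0–6, for the reasons shown in the working.

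The cost is a few lines of text and code and slightly more reporting, with no change to the instrument or sample size. The diffusion claim becomes a little more conservative.
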